### Ethics, study registration and consent

The final protocol was approved by the Ethics Committee of the Second Affiliated Hospital of Anhui Medical University (approval number: KY201406). The trial protocol was registered with the Clinicaltrials.gov protocol registration system (identifier: NCT02197481). All patients who are scheduled for liver resection at the Department of General Surgery, The Second Affiliated Hospital of Anhui Medical University and The First Affiliated Hospital of Anhui Medical University will be screened for eligibility and written informed consent. The study procedure, benefits, risks and data management will be clarified in detail during the preoperative conversation.

### Trial interventions

#### Group A: clamp crushing technique

In the clamp crushing technique group, the parenchymal transection is crushed using Kelly clamps (Geister, Badenia-Wirtembergia, Germany), progressive hemostasis of the vessels with titanium clips (Johnson&Johnson, Chihuahua, Mexico) or ligations, and coagulation by argon beam or electrocauterization **(** ERBE Elektromedizin, Tübingen, Germany**)**. Small vessels (≤1 mm) and minor oozing are controlled with bipolar electrocautery **(** ERBE Elektromedizin, Tübingen, Germany**)**. All other structures, including major intrahepatic bile ducts, are ligated or sutured.

#### Group B: BiClamp forceps hepatectomy

The power of the BiClamp forceps (Figure 2) is set to level four. The underlying liver tissue is divided, and the vessels ≤2 mm in diameter are sealed using the BiClamp forceps. The Glissonian sheaths or hepatic veins with a diameter larger than 3 mm are ligated and divided in the conventional manner to reduce postoperative bile leakage and intraoperative blood loss.

**Figure 2 Fig2:**
[figure not shown]
BiClamp forceps liver transection. **A** BiClamp forceps; **B** The surgical process of hepatectomy by BiClamp forceps.

### Primary and secondary endpoints

#### Primary endpoint

The primary efficacy endpoint of the trial will be the total intraoperative blood loss using the randomized dissection technique, which is defined as blood loss from the beginning of the surgical procedure (skin incision) to the end of the surgical procedure (closure of the skin). The amount of blood loss is estimated by including the amount of blood collected in the suction containers, weighing the soaked swabs after subtracting the rinse fluids and ascites, and weighing the dry swabs that were used during operation (assuming that 1 ml of blood is equal to 1 g).

#### Secondary endpoints

Secondary outcomes will be operation time; liver transection time; transection speed; total blood loss per unit transection area; incidence and amount of intraoperative blood transfusion, reoperation and hepatic injury; duration of postoperative hospital stay; mortality; total hospitalization expenditure; and general (wound infection and pulmonary infection) and liver resection associated postoperative morbidity (biliary leakage, post-hepatectomy liver failure and post-hepatectomy hemorrhage) will be assessed (Table 1).

**Table 1 Tab1:** **Definition of secondary endpoints**

**Secondary endpoint**	**Definition and assessment of outcomes**
Operation time	Time from incision to end of skin closure (minutes)
Liver transection time	Time from beginning to end of liver resection (minutes)
Liver transection area	Area estimated using Adobe Photoshop 7.0 (Adobe System Inc., San Jose, CA, USA) computer software, from the shape of the transection plane, which was traced onto a paper sheet at the end of liver resection (cm^2^)
Liver transection speed	Speed calculated as the transection area divided by the transection time (cm^2^/min)
Total blood loss per unit transection area	Blood loss calculated as the total blood loss divided by the transection area (ml/ cm^2^)
Intraoperative blood transfusion	The indications for blood transfusion were massive hemorrhage (>1,500 ml) during surgery or a hemoglobin level <7 g/dl within stable hemodynamic measures.
Postoperative hospital stay	Time from day of operation until discharge (days)
Total hospitalization expenditure	Costs from admission to discharge ($)
Postoperative liver injury	Serum levels of the aspartate aminotransferase, alanine aminotransferase, bilirubin, albumin and international normalized ratio on postoperative days one, three, five and seven
Mortality	Death due to any cause until 90 days after the operation and the reason
Morbidity	Postoperative complications will be recorded until 90 days after operation. The severity of complications will be graded according to the Clavien-Dindo classification [17].
	Biliary leakage: the international study group of liver surgery (ISGLS) definition (grade A, B or C) [18]
	Post-hepatectomy liver failure: ISGPS definition (grade A, B or C) [19]
	Post-hepatectomy hemorrhage: ISGPS definition (grade A, B or C) [20]
	Intra-abdominal fluid collection or abscess: any imaging modality detecting an intra-abdominal fluid collection associated with abdominal discomfort or pain, or elevation of infectious parameters.
	Pneumonia: infection of the lung with evidence of increased infection parameters (C-reactive protein >2 mg/dl and/or leukocytes >100,000/ml) not caused by a different pathologic process or evidence of pulmonary infiltration on a chest X-ray, requiring antibiotic therapy.

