## Background

Minimization of blood loss during liver resection remains a major concern for hepatic surgeons due to the correlations among excessive hemorrhage, requirement of blood transfusions, higher morbidity and mortality rates and poor long-term outcomes [1-3]. In the last few decades, various techniques have been adopted to decrease intraoperative blood loss during hepatectomy, including inflow occlusion and low central venous pressures. Assuming that inflow occlusion and low central venous pressure (CVP) anesthesia cause significant damage via ischemia and reperfusion [4,5], the method applied for hepatectomy has been considered to be the most critical factor influencing intraoperative blood loss [6].

Since the clamp crushing technique was introduced in the 1980s [7], numerous high-tech equipment has been developed to improve parenchymal transection [8-10]. Randomized clinical trials and a recent meta-analysis have shown that these modern devices result in similar blood loss and transfusion requirements compared to the clamp crushing technique, but with a higher cost due cost of the device and disposable medical apparatus [6,8-10]. The optimal method for liver parenchymal division to obtain minimal blood loss is controversial. Therefore, hepatic surgeons still select the method for liver transection according to their own preferences.

Bipolar vessel sealing (BiClamp® forceps, ERBE Elektromedizin, Tübingen, Germany) is a novel hemostatic device that can seal large tissue bundles and blood vessels up to 7 mm in diameter. The BiClamp forceps resist repetitive autoclaving sterilization, which reduces health care costs and medical waste. In a randomized clinical trial, the application of BiClamp forceps significantly decreased operation time, blood loss and costs in patients undergoing mastectomy and vaginal hysterectomy [11,12]. Our retrospective analysis has provided primary evidence for BiClamp forcep efficacy and safety for liver transection [13]. However, the retrospective non-randomized design of this study could not draw a definitive conclusion. Therefore, we conduct this randomized controlled trial to verify the superiority of the BiClamp forceps during liver transection.

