### Eligibility criteria

#### Inclusion criteria

Patients who meet the following criteria will be included in the study:Above 18 years of age,Elective hepatic resection due to benign or malignant hepatobiliary disease,Child-Pugh class A or B liver function andInformed consent.

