#### Randomization

To achieve comparable groups in terms of known and unknown risk factors, randomization will be performed. The allocation schedule will be generated by computer-generated random numbers, with an allocation ratio of 1:1 equal probability of assignment to each group. All patients will be randomized using consecutively numbered opaque envelopes sealed by the investigators. Envelopes will be opened upon entrance of the patient to the operating room.

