### Statistical analysis

The two-sided null hypothesis for the primary outcome measure states that both study interventions lead to similar total intraoperative blood loss; the alternative hypothesis is that one intervention performs better than the other. This null hypothesis will be tested by application of an analysis of covariance that adjusts for the transection surface area, CVP, preoperative international normalized ratio (INR) and preoperative platelet count.

Background characteristics and surgical outcome measures will be compared using Fisher’s exact tests or chi-squared for categorical data, and Student’s t-test for continuous variables. Categorical data will be presented as frequencies and group percentages, and continuous variables will be expressed as the means and standard deviations. The homogeneity of the two groups will be described by comparing the demographic data and baseline values. All analyses will be performed on an ITT basis [16]. For the ITT analysis, data will be processed for all trial patients in the groups in which they are randomized. Statistical significance is defined as *P* <0.05. All statistical calculations will be performed with the help of SPSS10.0 (SPSS, Chicago, USA).

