## Discussion

Since the introduction of the clamp crushing technique in 1973 [7], this technique has become the gold standard for liver parenchymal transection due to its effectiveness in controlling blood loss, reduction in operative time and low cost. A variety of devices have been developed to improve parenchymal transection in the past 10 to 15 years [8-10]. However, many randomized studies have failed to show any significant advantage over the clamp crushing technique [8-10]. BiClamp forceps, a reusable bipolar sealing instrument, has been available for open surgery procedures since 2002 [11]. Our retrospective data from between July 2007 and July 2014 has shown a significant reduction in blood loss and lower costs in patients operated on using BiClamp forceps. Based on these results, the first randomized controlled trial is designed to evaluate the efficacy, safety and cost-effectiveness of BiClamp forceps compared to the clamp crushing technique during elective hepatic resection.

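### Minor, secondary endpoint: the expenditure endpoint counts from admission, so spending before randomisation adds variance to the cost comparison without biasing it

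*Protocol article*

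**What the plan says.** In the protocol article, Table 1 (Definition of secondary endpoints) defines total hospitalization expenditure, in dollars, as "Costs from admission to discharge". It lists no components and no split by period.

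The Randomization section says: "Envelopes will be opened upon entrance of the patient to the operating room". The Inclusion criteria admit patients for "Elective hepatic resection due to benign or malignant hepatobiliary disease", so these are planned operations with admission ahead of surgery.

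The Statistical analysis section reserves covariate adjustment for the primary outcome, blood loss. Surgical outcome measures that are continuous get "Student’s t-test for continuous variables", with no adjustment mentioned.

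Cost matters to the trial's stated purpose. The Discussion says that the trial is designed to "evaluate the efficacy, safety and cost-effectiveness of BiClamp forceps compared to the clamp crushing technique", and the Background presents the instrument's reusability as a saving.

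**The concern.** A patient's bill up to the moment the envelope is opened (work-up, imaging, preparation, preoperative bed days) is settled before the arms exist. The technique cannot change it, yet it is part of the outcome. In an unadjusted comparison it acts as noise: it widens the confidence interval for the cost difference and lets chance imbalance in earlier spending appear as a difference between techniques.

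What is at stake is the precision of one secondary endpoint. The primary analysis and patient safety are untouched. The point deserves a line because cost-effectiveness is a declared aim and the remedy is cheap.

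**Working it through.** **Order of events.** Admission comes first, then operating-room entry with the envelope opened, then operation and discharge. The cost window opens at the first step and randomisation happens at the second. For an elective patient, everything billed between the two is pre-randomisation cost.

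**Bias.** Write total cost as T = B + A, with B the cost before randomisation and A the cost after it. Under randomisation the expected between-arm difference in B is zero, so the expected difference in T equals the expected difference in A. Both windows estimate the same effect.

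**Precision.** Let r = SD(B)/SD(A) and let rho be the correlation of B and A. Then

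Var(T)/Var(A) = 1 + r² + 2·rho·r.

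This exceeds 1 unless rho is below −r/2, so starting the count at randomisation normally removes variance.

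**Inputs.** The 48 per arm comes from the Abstract, and agrees with the total of 96 in the Patient involvement section. The article gives no cost SD, correlation or target cost difference, so r, rho and the effect size below are assumptions. Power is for a two-sided two-sample t-test at 5% with an assumed true cost difference of 0.6 SD(A). The effective number per arm is 48 divided by the inflation, and the effect size on the total is 0.6/√inflation.

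| r | rho | Variance inflation | Effective n per arm | Power |
|---|---|---|---|---|
| 0 (count from randomisation) | – | 1.00 | 48 | 83% |
| 0.1 | 0 | 1 + 0.01 = 1.01 | 48/1.01 = 47.5 | 83% (0.825 against 0.829) |
| 0.2 | 0 | 1 + 0.04 = 1.04 | 48/1.04 = 46.2 | 81% |
| 0.3 | 0 | 1 + 0.09 = 1.09 | 48/1.09 = 44.0 | 80% |
| 0.5 | 0.3 | 1 + 0.25 + 0.30 = 1.55 | 48/1.55 = 31.0 | 65% |

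**Second parameterisation.** Suppose a share s of total cost variance arises before randomisation and is independent of later cost. The standard error is then multiplied by 1/√(1−s). If a count from randomisation had 90% power, the admission total would have 88.5% at s = 5%, 86.8% at 10%, 82.6% at 20% and 77.4% at 30%. The direction is the same, and the size again depends entirely on an unknown.

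The plan has no figure to reproduce here: its only sample-size calculation is for blood loss, and it claims no power for expenditure.

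**The case against.** The strongest reply is that nothing here is wrong as written. The endpoint is named total hospitalization expenditure, and admission to discharge is what that name means. A whole-admission cost is a legitimate quantity for a payer. This stands: the definition is coherent, and preferring a later start is a design choice. What remains is that the choice gives up precision in the comparison for no gain in it, since the full total can be reported alongside.

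A second reply is that the loss may be trivial. The Standardization of perioperative care section applies one department's guidelines to both arms, so preoperative cost may vary little. This also stands, and is why the range starts at about 1%. The 55% end needs the highest ratio and the highest correlation considered to occur together.

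Two stronger readings are tempting and are not supported.

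- *The two resource endpoints contradict each other.* Table 1 counts hospital stay from the day of operation. But that endpoint is named postoperative stay, so its later start follows from its name. Different windows for differently named endpoints are not an inconsistency.
- *The endpoint favours BiClamp because a reusable device may be missing from a patient's bill.* The Background does say "The BiClamp forceps resist repetitive autoclaving sterilization, which reduces health care costs and medical waste", and the control arm uses "progressive hemostasis of the vessels with titanium clips", which would naturally be charged per patient. But the article never says that device cost is excluded. A hospital may bill a per-use fee, and costing rules are commonly left to the full protocol. The control arm also uses durable equipment (Kelly clamps, argon beam or electrocautery), so any omission could affect both arms. Neither the size nor the sign of a net effect can be derived.

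**Conclusion.** The point holds as a minor one on a secondary endpoint. The stated window puts pre-randomisation inpatient spending into an outcome tested without adjustment. This costs precision and introduces no bias.

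The size is not derivable from the article. Under the assumed inputs, variance inflation runs from negligible (about 1%) to substantial (about 55%); 48 patients per arm then carry the information of between about 47.5 and 31. These figures rest on assumed SD ratios of 0.1 to 0.5 and correlations of 0 to 0.3. The power figures rest in addition on an assumed difference of 0.6 postoperative SD. That admission precedes operating-room entry with some billed care in between is inferred from the elective setting; the article does not describe it.

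**What to change.** In Table 1, make the compared quantity cost from operating-room entry (or from the day of operation, if bills are dated only by day) to discharge. Keep the admission-to-discharge total as a descriptive line by arm.

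Alternatively, keep the admission total as the outcome and adjust for preoperative cost as a covariate. This estimates the same difference and removes the preoperative variance, together with whatever part of later cost it predicts.

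Either change needs a line in the article's definition or analysis text and no extra patients. The cost is that preoperative charges must be separated from the rest of each bill, which assumes that the billing records allow it. With the first option, the tested figure is also no longer the full admission total named in the study aim, which is why that total should still be reported.

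### The pneumonia definition's leukocyte cut-off of 100,000 per ml is only 100 per microlitre, so practically every patient passes the infection-marker test

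*Protocol article*

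**What the plan says.** The Secondary endpoints section of the protocol article names pulmonary infection as one of two general complications to be assessed: "general (wound infection and pulmonary infection". Table 1, in the Morbidity rows, defines pneumonia as "infection of the lung with evidence of increased infection parameters" and puts numbers on those parameters in brackets: "C-reactive protein >2 mg/dl and/or leukocytes >100,000/ml". The sentence then continues "not caused by a different pathologic process or evidence of pulmonary infiltration on a chest X-ray, requiring antibiotic therapy".

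This is the only leukocyte threshold in the article. The Table 1 row on intra-abdominal collections also refers to raised infectious parameters but gives no figures, so nothing elsewhere corrects the value or the unit.

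**The concern.** A cut-off for raised infection markers should lie near or above the upper end of normal. Leukocyte counts are ordinarily several thousand per microlitre, that is, several million per ml. A threshold of one hundred thousand per ml is therefore far below normal, and a patient with a normal or even severely reduced count is above it. Because the two markers are joined by and/or, the leukocyte limb suffices by itself, so the whole marker element is met.

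What is at stake is the objectivity of a named safety outcome. The marker limits are the only numerical criteria in the pneumonia definition. If they exclude nobody, an assessor must either apply an empty test or quietly substitute a private threshold. The first costs specificity and the second costs reproducibility.

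**Working it through.** **Inputs**

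- Leukocyte cut-off: above 100,000 per ml (Table 1, Pneumonia).
- Link between CRP and leukocytes: and/or, so either suffices (same row).
- Usual adult leukocyte count: not in the article. Assumed 4,000 to 10,000 per microlitre, with 3,500 to 11,000 as a wider range.

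The cut-off is a stated definition, not a derived figure, so there is no calculation of the plan's own to reproduce.

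**Step 1: convert the unit.** 1 ml = 1,000 microlitres, so 100,000 per ml ÷ 1,000 = 100 per microlitre, or 0.1 × 10⁹ per litre.

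**Step 2: compare with ordinary counts.** Ratio = (count per microlitre × 1,000) ÷ 100,000.

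| Count per microlitre | Count per ml | Multiple of the cut-off |
|---|---|---|
| 500 | 500,000 | 5 |
| 1,000 | 1,000,000 | 10 |
| 3,500 | 3,500,000 | 35 |
| 4,000 | 4,000,000 | 40 |
| 10,000 | 10,000,000 | 100 |
| 11,000 | 11,000,000 | 110 |

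Only a patient with 100 leukocytes per microlitre or fewer would fail the limb.

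**Step 3: try the obvious correction of the unit.** Read as per microlitre, the cut-off is 100,000 per microlitre, or 100 × 10⁹ per litre. Against an upper end of 10,000 that is 100,000 ÷ 10,000 = 10 times; against 11,000 it is 100,000 ÷ 11,000 ≈ 9.1 times. Almost no patient would reach it. Changing the unit alone therefore does not give a usable threshold: the number, or both number and unit, must be wrong.

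**Step 4: follow the logic through the definition.** Let L be a judged lung infection, M the marker element, N no other pathologic process, X an infiltrate on X-ray, and A antibiotic therapy required. The sentence can be read in more than one way:

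- X as an alternative to the markers: L and [(M and N) or X] and A. With M always true this becomes L and (N or X) and A.
- X as an alternative to the whole first part: [(L and M and N) or X] and A. This becomes [(L and N) or X] and A.
- X inside the clause on other causes: L and M and not (other process or infiltrate) and A. This becomes L and not (other process or infiltrate) and A.

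M drops out of all three. Under the first two readings a case can be counted with neither a raised marker nor an X-ray finding. The third would count an infiltrate against pneumonia, which can hardly be meant and shows why the sentence needs bracketing.

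**The case against.** The strongest reply is that this is a slip of digit or unit in a single item of a long secondary list. The governing words ask for increased parameters, so a sensible assessor would not count a normal leukocyte count as increased. Lung infection and antibiotic therapy are still required, so the error does not turn every patient into a pneumonia case. The definition is the same in both arms, the Blinding section says patients and outcome assessors are blinded, and complications are also graded by Clavien-Dindo, which does not use this cut-off. The 40- to 100-fold figure measures the size of the slip, not the number of misclassified cases.

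Most of this stands as a limit on the weight of the point. The primary endpoint (intraoperative blood loss) and the sample size are untouched. No mechanism favouring one technique has been shown, and no misclassification rate can be derived from the article. If CRP often exceeds 2 mg/dl after this surgery, which the article does not address, correcting the leukocyte limb alone may change few classifications.

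It does not rescue the text. An assessor who ignores the printed number in favour of the words around it is using an unstated threshold, which is what a numerical definition exists to prevent. The X-ray limb does not restore the marker test either, since adding an alternative to a condition that is always met excludes nobody. An extraction fault, such as a lost micro sign, is ruled out as an explanation by Step 3.

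**Conclusion.** The concern holds. As printed, the leukocyte limb is met by practically every patient, by a factor of 40 to 100 on the assumed usual range (35 to 110 on the wider one), and the and/or makes the whole marker element empty. The conclusion rests on an adult range that the article does not give, but it is insensitive to that assumption, since even 500 per microlitre is five times the cut-off. The article does not show whether the digit, the unit or both are at fault. The effect is confined to the specificity and reproducibility of one secondary safety component. It is an outcome threshold that is wrong as stated, not a detail left to a fuller document, and it should be corrected.

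**What to change.** Check the leukocyte cut-off against the source definition and the case report form, then restate both value and unit in Table 1. An upper limit of normal from the trial laboratory, expressed per microlitre, would be one way to word it. In the same edit, bracket the sentence so that it is clear whether the X-ray finding is an alternative to the markers or an additional requirement, and which elements are jointly needed. If the case report form repeats the printed figure, correct it there too. Because enrolment began on 1 October 2014, apply the corrected rule to all patients in both arms, including those already assessed.

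The cost is one line in Table 1 and, if needed, one in the case report form. No additional data are required.
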